
### Participant timeline {13}

A detailed timeline of enrolment, interventions (including any run-ins and washouts), assessments, and visits for participants is shown in Fig. 3.

**Fig. 3 Fig3:**
[figure not shown]
Time schedule of enrolment, interventions, and assessments

### Sample size {14}

All calculations were performed using PASS 15.0 (NCSS, LLC), with parameters verified by an independent statistician. The sample size calculation was based on detecting a clinically meaningful difference in the primary outcome of hypoxemia incidence (SpO_2_ < 90% for > 10 s) between study groups. From our pilot data, we anticipate a 50% incidence of hypoxemia in the control group receiving standard propofol sedation. We hypothesize that low-dose esketamine will achieve an absolute risk reduction of 15%, corresponding to a 35% hypoxemia incidence in the intervention group. Using a one-tailed *Z*-test for proportions (unpooled) with 80% power (*β* = 0.20) and a significance level of *α* = 0.025 (selected because esketamine’s established respiratory safety profile makes increased hypoxemia biologically implausible; detecting non-inferiority/superiority is the sole clinical priority.), we calculated a minimum requirement of 132 participants per group. To account for potential 10% attrition, we will enroll 147 participants per group (*N* = 294 total). This conservative approach ensures adequate power even if the actual control group incidence varies between 45 and 55% or if dropout rates reach 15%. The one-tailed design is appropriate given esketamine's established respiratory safety profile and the clinical irrelevance of detecting increased hypoxemia risk with this intervention.

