#### Objectives {7}

This trial aims to determine whether intravenous low-dose esketamine (0.25 mg/kg) reduces the incidence of hypoxemia (defined as SpO_2_ < 90% for > 10 s) by ≥ 15% compared to placebo during propofol-sedated gastroscopy in patients with moderate-to-high risk OSA (STOP-Bang score ≥ 3), using a one-sided *α* = 0.025.

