## Statistical methods

### Statistical methods for primary and secondary outcomes {20a}

All analyses will be conducted using SPSS 23.0 (IBM Corp) by a statistician blinded to group allocation. The primary outcome will be analyzed using a one-sided *Z*-test at *α* = 0.025, while secondary outcomes will employ two-sided tests with *α* = 0.05.

Continuous variables will be assessed using the Kolmogorov–Smirnov test examining for normality. Normally distributed data will be presented as mean ± standard deviation (SD). Non-normal data will be presented as median or interquartile range (IQR). Categorical variables will be presented as counts and percentages.

For the primary outcome of hypoxemia incidence, we will employ a one-sided Z-test for proportions to evaluate the hypothesized reduction in the esketamine group, reporting absolute risk differences with 95% confidence intervals. Secondary outcomes will be analyzed using appropriate statistical tests based on variable characteristics: continuous normally distributed variables will be compared using independent *t*-tests, while non-normal continuous data will be assessed with Mann–Whitney *U* tests. Categorical outcomes will be analyzed using *χ*^2^ tests or Fisher’s exact tests as warranted by sample sizes. For time-to-event outcomes such as duration of hypoxemic episodes, we will utilize Kaplan–Meier survival analysis with log-rank tests. Longitudinal physiological measurements including mean arterial pressure and heart rate will be evaluated using repeated measures ANOVA, with post hoc Bonferroni corrections applied to account for multiple comparisons while maintaining the overall type I error rate at *α* = 0.05. All comparative analyses will be conducted by a blinded statistician using SPSS version 23.0, with two-sided tests (*α* = 0.05) employed for all secondary outcomes to conservatively assess potential group differences.

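### The 132 per group matches one-sided α = 0.05, not the stated 0.025; true power is about 70–75%, not 80%, and the robustness claim fails

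*Protocol article*

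**What the plan says.** Sample size {14} gives every input. From pilot data, "we anticipate a 50% incidence of hypoxemia in the control group", and an absolute reduction of 15 points takes the esketamine group to 35%. The method is a one-tailed Z "test for proportions (unpooled) with 80% power" and "a significance level of *α* = 0.025". From these, "we calculated a minimum requirement of 132 participants per group", raised to 147 per group (294 in total) for 10% attrition. The section says that an independent statistician verified the parameters, and it adds: "This conservative approach ensures adequate power even if the actual control group incidence varies between 45 and 55% or if dropout rates reach 15" per cent.

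The significance level is the same elsewhere. Objectives {7} frames the hypothesis "using a one-sided *α* = 0.025". Statistical methods {20a} says: "The primary outcome will be analyzed using a one-sided *Z*-test at *α* = 0.025". Trial design {8} gives 1:1 allocation.

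**The concern.** The level, sidedness, effect and test are stated in full and agree across three sections, but the sample size does not follow from them. It looks as if the calculation was run at one-sided 0.05 while the test was specified at one-sided 0.025.

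This is the only sample-size justification for the primary outcome. If the trial has less power than stated, a real 15-point reduction, which the protocol treats as clinically meaningful, will be missed more often than the planned 20%. The Discussion expects negative findings to inform practice, and readers would weigh a null result as if it came from a trial with 80% power. The Interim analyses {21b} section also lets a committee consider enlarging the sample, and that decision should start from the true planning power.

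**Working it through.** **Inputs.** Sample size {14}: p₁ = 0.50, p₂ = 0.35, d = 0.15, unpooled one-tailed Z-test, power 80% (z = 0.842), α = 0.025 (z = 1.960). Trial design {8}: 1:1 allocation.

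**Formula.** n per group = (z_α + z_β)² × [p₁(1 − p₁) + p₂(1 − p₂)] / d². The bracket is 0.25 + 0.2275 = 0.4775, and d² = 0.0225.

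**Reproducing the stated figure.** With z_α = 1.645 (one-sided 0.05): (1.645 + 0.842)² × 0.4775 / 0.0225 = 131.2, so 132. This matches exactly. The attrition step is also right: 132 / 0.9 = 146.7, so 147.

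**At the stated level.** With z_α = 1.960: (1.960 + 0.842)² × 0.4775 / 0.0225 = 166.6, so **167 per group**, 35 more than stated. Other standard versions at one-sided 0.025 move further from 132: pooled variance 170, arcsine 170, continuity-corrected 180–183. The unpooled formula comes close to 132 at α = 0.025 only if power is set to 70% (n = 131).

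**Power at the planned size.** Power = Φ(d / √(0.4775 / n) − 1.960), for a fixed-sample test at one-sided 0.025:

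| n per group | Situation | d / SE | Power | Exact binomial |
|---|---|---|---|---|
| 147 | all enrolled analysed | 2.632 | 74.9% | 74.7% |
| 132 | 10% attrition | 2.494 | 70.3% | 70.7% |
| 125 | 15% dropout (147 × 0.85) | 2.427 | 68.0% | 67.1% |

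**Difference detectable with 80% power.** Keep the control rate at 50% and solve d = 2.802 × √([0.25 + p₂(1 − p₂)] / n) with p₂ = 0.50 − d. This gives 16.8 points at n = 132 and 15.9 points at n = 147.

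**The robustness sentence.** The protocol does not say what is held constant when the control rate moves, so three readings were tried at one-sided 0.025:

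| Held constant | n per group | Control 45% | Control 50% | Control 55% |
|---|---|---|---|---|
| 15-point reduction | 125 | 69.8% | 68.0% | 67.1% |
| 15-point reduction | 132 | 72.2% | 70.3% | 69.4% |
| 15-point reduction | 147 | 76.7% | 74.9% | 74.0% |
| Relative risk 0.70 | 132 | 62.5% | 70.3% | 77.8% |
| Relative risk 0.70 | 147 | 67.2% | 74.9% | 82.0% |
| Esketamine rate 35% | 132 | 38.5% | 70.3% | 91.5% |

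Power passes 80% only at the 55% end, under some readings. At 45% and at the base case it is below 80% under all of them. Even at one-sided 0.05, 15% dropout with 50% against 35% gives 78.3%.

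**The case against.** The arithmetic is not open to dispute, but four points bear on how much weight it carries.

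- **Which n is relevant.** The primary analysis is by intention to treat in all randomised participants, with imputation for missing data, and the outcome is measured during a procedure limited to 15 minutes. Loss of the primary outcome may be small, so 75% may be nearer the truth than 70%. That stands, and it is why the shortfall is best given as 5 to 10 percentage points. It does not bring the trial to 80%: full retention of 147 per group still falls short.
- **The meaning of the robustness sentence.** Adequate power is not defined and the effect held constant is not named, so no single set of figures is the only reading. That also stands. If adequate means the planned 80%, the sentence still fails, because the base case and the 45% end fail under every reading.
- **The interim look.** Interim analyses {21b} plans an unblinded half-way analysis that could lead to stopping or to a larger sample. The powers here are fixed-sample values and should be labelled so. A possible enlargement if the interim result disagrees with the hypothesis does not correct the planning figure.
- **The cause.** That 0.05 was entered in the software is an inference from an exact match. What is established is that 132 does not follow from the stated inputs.

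**Conclusion.** The concern holds. With the protocol's own inputs the requirement is 167 evaluable per group, not 132. At one-sided α = 0.025, the planned trial has about 70% power at 132 per group and about 75% if all 147 are analysed, so a true 15-point reduction would be missed about 30% or 25% of the time rather than 20%. The robustness statement is wrong as written.

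These figures assume a 50% control rate, a 15-point absolute reduction and a single fixed-sample analysis; exact binomial calculation agrees to within about one percentage point. The validity of the primary test is not affected, because the level is stated consistently. The error lies in the sample size and in the power claimed for it.

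**What to change.** In Sample size {14}:

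1. Keep one-sided α = 0.025 and N = 294. State fixed-sample power for 50% against 35% as about 70% with 132 evaluable per group and about 75% if all 147 are analysed.
2. State the difference detectable with 80% power as 16.8 points at 132 per group and 15.9 points at 147.
3. Delete the sentence on 45–55% control incidence and 15% dropout. If it is replaced, name the effect held constant and give the matching figures; with a 15-point reduction these are 69–72% at 132 per group and 67–70% at 125.
4. Do not move α to 0.05 to recover the 132. That would double the type I error and contradict the objective and the analysis section.

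The cost is wording only, here and in the registry entry if it carries the same figures. No patients are added, but the stated power becomes less favourable.

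If the sponsor prefers to hold 80% power, the size is 167 evaluable per group, or 167 / 0.9 = 185.6, so 186 randomised per group and 372 in total, 78 more than planned. The protocol article gives recruitment as open until December 31, 2026, so either course can be settled before the results are known.

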### Recruitment {15}

In order to achieve adequate participant enrollment to reach target sample size, we have strengthened the recruitment plan to ensure SPIRIT compliance by (1) implementing a two-step screening process (electronic schedule review + pre-anesthesia STOP-Bang assessment) supervised by a dedicated coordinator; and (2) establishing tiered contingency plans (weekend slots) triggered if enrollment falls below 80% of targets. Monthly DSMB reviews will monitor progress, with all procedures emphasizing voluntary participation.

## Assignment of interventions: allocation

### Sequence generation {16a}

The allocation sequence will be computer-generated by an independent biostatistician using stratified block randomization (SAS 9.4). Stratification will be based on two clinically relevant factors: age group (18–65 years vs. > 65 years) and OSA severity (STOP-Bang score 5–6 vs. ≥ 7). Variable block sizes (4, 6, 8) will be used to enhance unpredictability, with details stored in a password-protected file accessible only to the trial statistician and DSMB chair. This ensures allocation concealment and prevents selection bias.

Roles are strictly separated to maintain blinding and prevent bias: sequence generated by an independent biostatistician, enrollment and consent completed by GCP-certified investigator, and intervention assigned by unblinded anesthesia nurse for prepares and dispenses study drugs per SNOSE system. The structured approach aligns with CONSORT and SPIRIT guidelines, ensuring robust randomization and minimizing bias.

### Concealment mechanism {16b}

The complete randomization scheme (including block sizes) will remain concealed in a restricted-access file. Emergency unblinding materials (sealed envelopes) will be attached to each participant’s CRF, accessible only to the chief anesthesiologist in case of serious adverse events.

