## Assignment of interventions: blinding

### Who will be blinded {17a}

This study will be conducted in a double-blind manner where the patients, endoscopists, anesthesiologists responsible for intraoperative care, and outcome assessors will all be blinded to the group assignment.

All study drugs will be prepared by an independent anesthesiologist who is not involved in the subsequent anesthesia management, data collection, or outcome assessment. This anesthesiologist will have access to the randomization schedule.

Both the esketamine and the placebo (0.9% normal saline) will be drawn up to identical volumes of 10 mL in identical 20-mL sterile syringes. The syringes will be wrapped in opaque foil to prevent any visual distinction between the two solutions. The wrapped syringes will be labeled only with the patient’s study identification number.

The prepared, blinded syringe will be handed to the procedural anesthesiologist immediately before the initiation of anesthesia. This anesthesiologist will administer the study drug as a bolus without knowing its content.

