### Procedure for unblinding if needed {17b}

Emergency unblinding is permitted only for suspected serious adverse reactions (SAEs). The principal investigator (PI) will hold the randomization list and be responsible for unblinding if necessary. All such events will be documented within 24 h to the IRB. Sealed envelopes attached to CRFs will reveal allocation.

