## Data collection and management

### Plans for assessment and collection of outcomes {18a}

All outcomes will be systematically assessed, collected, and recorded on CRFs by blinded assessors across three phases: baseline demographics (age, sex, BMI), clinical characteristics (ASA status, STOP-Bang score, Difficulty in mask ventilation [DMV] risk factors), and room-air SpO_2_ will be collected pre-procedure; continuous vital signs (HR/SpO₂/NBP recorded every 30 s), propofol requirements, hypoxemia episodes (SpO_2_ < 90% > 10 s), procedure/recovery times, and adverse events (graded by blinded assessors) collected intraprocedure; Satisfaction (10-cm VAS), PACU recovery metrics (MOAA/S = 5 time), and AEs (graded 1–3 for severity/causality) collected post-procedure.

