### Plans to promote participant retention and complete follow-up {18b}

To ensure high retention rates and complete follow-up data collection, the following strategies will be implemented: (1) clear consent discussions with visual aids emphasize study importance; (2) fixed anesthesia team and real-time CRF completion minimize errors; (3) immediate PACU assessments precede discharge, with small compensation (meal vouchers) offered. Withdrawals are documented without care penalties, and all collected data are retained for ITT analysis. Quarterly DSMB reviews monitor retention rates, with protocol deviations logged for sensitivity analyses. All data will be recorded in CRFs. Missing data (< 5%) will use mean imputation, analyzed via both ITT and per-protocol approaches. CRFs are publicly accessible via trial registry (ChiCTR2500099420).

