### Confidentiality {27}

All participant data will be handled with strict confidentiality measures, collected by designated anesthesiologists and follow-up physicians, immediately recorded in password-protected electronic CRFs. Original records (medical charts, consent forms, CRFs) stored securely for 10 years. Electronic data are encrypted and accessible only to study statisticians. De-identified data could be shared with DSMB for monitoring, with no public release until trial completion and publication. Physical documents are shredded after 10 years per hospital policy, and electronic archives are permanently deleted.

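### Code-break envelopes are attached to the CRFs that blinded assessors complete, and the CRF medium and the role that unblinds are not stated consistently

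*Protocol article*

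**What the plan says.** On where the individual codes are kept, Concealment mechanism {16b} states: "Emergency unblinding materials (sealed envelopes) will be attached to each participant’s CRF". It limits access to the chief anesthesiologist, when a serious adverse event occurs. Procedure for unblinding if needed {17b} confirms the location: "Sealed envelopes attached to CRFs will reveal allocation". The same section also has the principal investigator hold the randomization list and take responsibility for unblinding.

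On who uses the CRF, Plans for assessment and collection of outcomes {18a} states: "All outcomes will be systematically assessed, collected, and recorded on CRFs by blinded assessors". Who will be blinded {17a} requires that "outcome assessors will all be blinded to the group assignment".

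On the medium, Confidentiality {27} says that data are "immediately recorded in password-protected electronic CRFs", and Data management {19} also speaks of electronic collection. Yet {27} lists CRFs with charts and consent forms among the original records and has physical documents shredded after 10 years. Section {19} describes entry into REDCap by blinded staff with 10% double entry, which suggests transcription from paper.

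On the randomization material, Implementation {16c} keeps the allocation envelopes opaque and in a locked cabinet, reachable only by an unblinded nurse who does not assess outcomes. Sequence generation {16a} limits access to the sequence file to the trial statistician and the DSMB chair.

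**The concern.** A code-break envelope holds the same information as a randomization envelope. If it is fixed to the form on which outcomes are written, the allocation travels with the people who are meant not to know it.

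Blinded recording matters in this trial. The primary event is saturation below 90% for more than 10 seconds, while {18a} has vital signs recorded every 30 seconds. That 30-second series cannot by itself show whether a dip lasted longer than 10 seconds, so the primary endpoint leans on the hypoxemia episodes that are recorded separately. Airway intervention, movement requiring restraint and the grading of adverse events also call for judgement.

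The second issue is practical. A paper envelope cannot be attached to an electronic form. If the CRFs are electronic, the envelope route in {16b} and {17b} does not work as described, and staff would have to know which other route applies and who may use it.

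**Working it through.** The plan gives no figure on this point and no arithmetic applies. The check is a comparison of sections.

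1. **Envelope and form.** {16b} and {17b} attach the envelope to the participant's CRF. {18a} has blinded assessors record on CRFs. Nothing in these sections separates the envelope from the assessor physically. The stated barriers are the seal and the access rule.

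2. **What {18b} adds.** Under retention, {18b} refers to "fixed anesthesia team and real-time CRF completion minimize errors". This places CRF completion at the procedure, but it does not name the person who completes the form. The link between assessor and form rests on {18a} alone, which is sufficient.

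3. **The protocol's own standard.** {16c} gives the randomization envelopes opacity, a locked cabinet and a custodian outside outcome assessment. {16b} describes the code-break envelopes only as sealed and gives them none of these safeguards.

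4. **Two cases for the medium.**
   - Paper CRFs: the envelope sits with the assessors' form, and the weakness in step 1 applies to each of the 294 planned participants.
   - Electronic CRFs: there is nothing to attach an envelope to. The weakness in step 1 does not arise in that form, but the envelope route cannot be carried out as written. The principal investigator's list in {17b} is then the stated route.

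   The two cases exclude each other for a given CRF. Sections {19} and {27} contain signs of both, so the text does not settle which applies. Neither case leaves the present wording satisfactory.

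5. **Who unblinds.** {16b} reserves the envelope for the chief anesthesiologist, while {17b} makes the principal investigator responsible. The article does not say that these are the same person or how the two roles relate.

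6. **Who holds the list.** {17b} gives the list to the principal investigator. {16a} restricts the sequence file to the trial statistician and the DSMB chair. Both cannot be exact.

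**The case against.** The strongest reply is that attaching a sealed envelope does not give anyone permission to open it. Access is limited to one role and one trigger, and nothing shows that any assessor has learned an allocation. That stands: a reader might infer that the blind is broken, and the documents do not support it.

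A reader might also infer that, with electronic CRFs, no emergency unblinding route exists. That is wrong, because {17b} provides the principal investigator's list. Only the envelope route would fail.

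Nor do the documents support saying that an improper opening would go unnoticed. A broken seal may be visible, and {23} provides quarterly independent audits with unannounced inspections and a check of 10% of CRFs against source. However, no check of the seals is stated. The reporting to the IRB within 24 hours in {17b} documents emergency unblinding that is declared; it would not by itself reveal an undeclared opening.

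For the primary outcome, {5d} provides an independent Endpoint Adjudication Committee. This is a real safeguard, but it covers primary outcomes only. Airway intervention, restraint and adverse event grading remain with the assessors.

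Finally, one could try to put a number on the bias. The documents give no rate at which codes might become known and no share of borderline episodes, so any false-positive rate would merely reflect the assumptions chosen.

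**Conclusion.** The concern holds as an avoidable weakness in the protection of assessor blinding, together with an inconsistency that needs reconciling. If CRFs are paper, the seal and the access rule are the only stated barriers between blinded assessors and each participant's allocation, with adjudication and audit as partial safeguards. If CRFs are electronic, the envelope route does not work as written and the list held by the principal investigator remains. In either case the role that unblinds and the holder of the list are stated inconsistently.

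No size of bias is claimed. The conclusion rests on reading the CRF in {16b} and {17b} as the same form that assessors complete under {18a}; the article uses one term for both and makes no distinction. The change is worth making because it is specific and cheap, and because the protocol already applies the better safeguard to its randomization envelopes.

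**What to change.** - In {16b} and {17b}, delete the attachment to CRFs. Keep numbered, tamper-evident code-break envelopes in a secure place apart from the CRFs and out of the assessors' reach, but available whenever sedation is given.
- Log every opening with time, reason and role, and check all seals at database lock.
- State one CRF medium across {16b}, {17b}, {19} and {27}. If paper forms are transcribed into REDCap, say so.
- Reconcile the role that unblinds between {16b} and {17b}, and the holder of the randomization list between {16a} and {17b}.

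The cost is some rewording, moving the envelopes and keeping a log. The one downside is that the envelope must be fetched in an emergency, so its location has to be chosen with that in mind. The Trial status section plans recruitment to December 31, 2026, so a change made before then would protect the participants still to be enrolled.
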